## Abstract

**Background:**

Incisional hernia is a frequent complication following loop ileostomy reversal. Incisional hernias are associated with morbidity, loss of health-related quality of life and costs and warrant the investigation of prophylactic measures. Prophylactic mesh implantation at the time of surgical stoma reversal has shown to be a promising and safe method to prevent incisional hernias in this setting. However, the efficacy of this method has not yet been investigated in a large multicentre randomised-controlled trial (RCT) with adequate external validity. The P.E.L.I.O.N. trial will evaluate the efficacy of prophylactic mesh reinforcement after loop ileostomy closure in decreasing the rate of incisional hernia versus standard closure alone.

**Methods:**

P.E.L.I.O.N. is a multicentre, patient- and observer-blind RCT. Patients undergoing loop ileostomy closure will undergo intraoperative 1:1 randomisation into either abdominal wall closure with a continuous slowly absorbable suture in small-stitch technique without mesh reinforcement (control group) or abdominal wall closure with an additional reinforcement with a retromuscular non-absorbable, macro-pore (pore size ≥ 1000 μm or effective porosity >0%) light-weight monofilament or mixed structure mesh. A total of 304 patients (152 per group) will need to be randomised in the study. Based on inclusion and exclusion criteria, 1,014 patients are expected to be screened for eligibility in order to recruit the necessary number of patients. The primary endpoint will be the frequency of incision hernias within 24 months according to the European Hernia Society definition. Secondary endpoints will be the frequency of surgical site occurrences (including surgical site infections, wound seromas and hematomas, and enterocutaneous fistulas), postoperative pain, the number of revision surgeries and health-related quality of life. Safety will be assessed by measuring postoperative complications ≥ grade 3 according to the Dindo-Clavien classification.

**Discussion:**

Depending on the results of the P.E.L.I.O.N. trial, prophylactic mesh implantation could become the new standard for loop ileostomy reversal.

**Trial registration:**

DRKS00027921, U1111-1273-4657

**Supplementary Information:**

The online version contains supplementary material available at 10.1186/s13063-023-07089-3.

## Administrative information

Note: the numbers in curly brackets in this protocol refer to SPIRIT checklist item numbers. The order of the items has been modified to group similar items (see http://www.equator-network.org/reporting-guidelines/spirit-2013-statement-defining-standard-protocol-items-for-clinical-trials/).

## Introduction

### Background and rationale {6a}

Diverting loop ileostomy is used in colorectal surgery to reduce the consequences of leakage of a bowel anastomosis. According to the Federal Statistical Office of Germany, approximately 15,000 diverting loop ileostomies and 11,500 loop ileostomy closures are performed annually in Germany [1]. The timepoint of ileostomy reversal is debated [2, 3]. Parastomal hernia is frequent after ostomy creation and is estimated to be over 30% by 12 months, 40% by 2 years and 50% or higher at longer duration of follow-up [4, 5]. After primary closure of ileostomy sites, approximately 20% of patients develop an incisional hernia (IH) at the site of stoma reversal within 12 months and up to one-third within 2 years [6] as the incidence of IHs increases over time [7].

Multiple studies have shown that IH causes substantial morbidity and a reduction in the quality of life due to abdominal pain and discomfort, a reduction in the daily activity as well as mortality [8]. Furthermore, IH can cause potentially life-threatening complications with bowel incarceration and strangulation. Furthermore, recurrence of IH following IH repair, which occurs in up to 40% of patients [9], is associated with decreased quality of life [10]. IH causes a substantial burden to healthcare systems worldwide [11, 12]_ and an estimated annual cost of 8.2 million € for the German healthcare system [13].

Because of the important consequences for patients and national healthcare systems, the prevention of incisional hernia has been a subject of intensive investigation over the last decades. For ventral IHs, prophylactic mesh placement at the time of abdominal wall closure is now an accepted technique. Its efficacy has been tested in numerous randomised controlled trials (RCTs) [13–15].

For ostomy reversal, much less evidence is available. Probably because concerns of safety have been voiced regarding an increased risk of surgical site infections (SSI) and mesh infections. Three non-randomised studies have been published on prophylactic mesh placement for ostomy reversal [16–18]. Overall, these three studies showed an overwhelming reduction of IH in the prophylactic mesh group compared to no mesh placement in a systematic review (OR 0.10, 95% CI 0.04–0.27, *p* < 0.001, I2 = 0%, CI 0–91.40%) [19]. However, two of the three studies were retrospective analyses, none of the studies was randomised, follow-up and endpoint assessment were inadequate and studies were at high risk of bias [19]. Furthermore, the technique varied widely between the studies. However, none of the studies showed an increase in the rate of SSI for patients undergoing prophylactic mesh placement at the site of stoma reversal, thus indicating the safety of the technique.

In addition, one recent RCT trial (ROCSS, NCT02238964) compared prophylactic mesh placement in an intraperitoneal onlay position (IPOM) at the time of ostomy reversal to primary closure [20]. In total, 790 patients were 1:1 randomised. The clinically detectable hernia rate, the primary outcome, at 2 years was 12% (39 of 323) in the mesh group and 20% (64 of 327) in the control group (adjusted relative risk [RR] 0.62, 95% CI 0.43–0.90; *p*=0.012). Furthermore, no significant differences were seen in wound infection rate, seroma and serious adverse events, underlining the safety of prophylactic mesh placement. There were, however, considerable differences to the P.E.L.I.O.N trial. First, ROCSS used an industry-sponsored biological absorbable mesh, that is uncommon in hernia surgery and associated with considerable costs. The postulated advantages of a biological mesh over synthetic meshes have so far not been proven in larger controlled trials. On the contrary, a review on mesh selection for ventral hernia repair and incisional hernia prophylaxis draws the conclusion that the use of biological meshes can currently not be recommended [14]. A recent RCT showed that biological meshes are inferior to polypropylene meshes in ventral IH repair [21]. Second, the mesh was placed in an intraperitoneal onlay position (IPOM) rather than in a sublay position as in the P.E.L.I.O.N trial. Third, the primary outcome parameter was IH at 2 years evaluated by clinical exam only. The European Hernia Society (EHS), however, recommends IH evaluation by clinical as well as radiological exams within 24 months. Only a subgroup of patients in the ROCSS study underwent radiological examination and only within a limited follow-up period of 12 months [20]. For this subgroup, results confirmed the findings for the primary endpoint: IH was 20 (9%) of 229 in the prophylactic mesh group vs 47 (21%) of 226 for the control group (adjusted RR 0.42, 95% CI 0.26–0.69; *p*<0.001) [20]. Fourth, ROCSS included all types of stomata (end, loop, colostomy, ileostomy) and not only loop ileostomies as in the P.E.L.I.O.N trial. Finally, the abdominal wall closure in the control group was not standardised nor reported in the trial, raising a relevant concern of a potential bias. Fascial closure technique has an effect on incisional hernia rate, as shown for example by the STITCH trial [22]. In summary, considerable differences exist between ROCSS and the P.E.L.I.O.N trial.

## Objectives {7}

The high rate of IH after loop ileostomy closure with its associated morbidity, loss of health-related quality of life and costs (hernia repair, loss of workforce) warrants the investigation of prophylactic measures. Prophylactic mesh implantation at the time of surgical stoma reversal has shown to be a promising and safe method to prevent IH formation in this setting. However, the efficacy of this method has not yet been investigated in a large multicentre RCT with adequate external validity. P.E.L.I.O.N will fill this evidence gap. The aim of the PELION trial is to evaluate the efficacy of prophylactic mesh reinforcement after loop ileostomy closure in decreasing the rate of IH versus standard closure alone.

## Trial design {8}

P.E.L.I.O.N is a randomised controlled observer- and patient-blinded multicentre surgical superiority trial with two parallel study groups.

## Methods: participants, interventions and outcomes

### Study setting {9}

The study will be carried out in 10 high-volume academic hospitals in Germany. A list of study sites can be found in Supplement 1.

### Eligibility criteria {10}

#### Inclusion criteria for patients

To obtain a homogenous but still representative patient population for analysis and high-external validity, all patients with primary loop ileostomy closure and without further interventions or conditions to the abdominal wall, which might interfere with the primary outcome measure and reduce the reproducibility and interpretability of the data, are eligible for inclusion and will be informed about the P.E.L.I.O.N. trial:Planned elective loop ileostomy closureAdult patients (≥ 18 years of age)Life expectancy > 2 yearsWritten informed consentAbility to understand the character and individual consequences of the clinical trial

#### Exclusion criteria for patients

American Society of Anesthesiologist (ASA) physical status class ≥ 4Infected/septic surgical site (risk for surgical site occurrences (SSO) of grade 4 according to Ventral Hernia Working Group (VHWG) classification) (see Supplement 2)Presence of parastomal hernia in loop ileostomy site with fascia defect > 8cm (Table 1)Presence of a concomitant incisional hernia that impedes loop ileostomy reversal or placement of the mesh at the ileostomy site (Table 1)Patients with prior mesh placement on site of ileostomyChronic renal failure under haemodialysis/peritoneal dialysisPatients under strong immunosuppression or other medications likely to impede wound healing as judged by the operating surgeon. Examples of strong immunosuppression are:Steroid therapy ≥ 10 mg/dayTherapy with antitumor necrosis factor α (anti-TNF-α) within the last 4 weeksTherapy with everolimus or sirolimus within the last 4 weeksTherapy Avastin within the last 4 weeksCongenital haemorrhagic diathesis with need of perioperative treatmentParticipation in another interventional trial with interference on intervention and primary outcome of this trial

**Table 1 Tab1:** Details of exclusion criteria 3 and 4

Clinical exam	Radiological exam	Decision
The presence of a parastomal hernia or incisional hernia is *excluded* on the clinical exam	Not necessary	The patient **can** be included in the trial
Presence of a parastomal hernia > 8 cm or incisional hernia that would impede loop ileostomy reversal or placement of the mesh at the ileostomy site *confirmed* on clinical exam	Not necessary	The patient **cannot** be included in the P.E.L.I.O.N trial
Presence of a parastomal hernia or incisional hernia on clinical exam, but **unclear** whether: - Parastomal hernia is smaller or larger than 8 cm - Or if unclear whether incisional hernia impedes loop ileostomy reversal or placement of the mesh at the ileostomy site	Radiological exam (ultrasound or other) indicated	Inclusion/exclusion depends on radiological results

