### Sample size {14}

Sample size calculation is based on the rate of the primary endpoint (IH rate) within 24 months after surgery. Based on the assumption that the percentage of patients developing an IH in the control group is 30% (4–7), we hypothesise a reduction to 15% in the intervention arm (conservative reduction rate below that reported in the above-mentioned trials). Consequently, a sample size per group of 121 patients is needed for the group comparison by the chi-squared test to achieve 80% power in detecting this difference in IH rate at a two-sided level of significance of 5%. It is assumed that using a logistic regression model adjusting for IH risk (low-risk vs. high-risk patients: BMI ≥ 27) and including centre as a random effect in the primary analysis will lead to less unexplained variance and thus to an increased power.

The intercurrent event re-laparotomy affecting the loop ileostomy closure site and death without prior observation of IH are expected to be very rare, with just a few patients each. Based on previous trials, to account for the loss of information, a rate of 20% of dropouts, loss to FU and relevant ICEs (handled with the hypothetical strategy) is considered. Therefore, a total of 304 patients (152 per group) will be randomised. The other ICEs are ignored in the primary estimand and not accounted for in the sample size calculation. Calculation was performed using PASS 16.0.12. Only high-volume trial sites committing to include at least 10 patients per year will be chosen as trial sites.

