## Assignment of interventions: allocation

### Sequence generation {16a}

To ensure equal distribution of patient characteristics, randomisation will be used. Allocation of treatments will be performed using a web-based randomisation tool (www.randomizer.at). Block-wise randomisation will be conducted. Randomisation will be stratified by centre.

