The IH rates will be compared via a mixed logistic regression model including the factors treatment group and IH risk (high vs. low) as fixed effects and centre as a random effect. As the number of centres is relatively large in relation to the sample size, inclusion of the centre as a random effect instead of a fixed effect is indicated. Differences between centres cannot be ruled out but are of no special interest in the primary analysis; inclusion of centre as the random effect is recommended [38]. Besides this, the interpretation is more straightforward because “[…] in the context of RCTs, centre effects can be regarded as a nuisance parameter, as the primary goal is to estimate the treatment effect”. For the structure of the covariance matrix of the random intercept of centre, a variance component structure is used allowing for different variability within each centre while assuming that centres are independent. Missing data for the primary outcome variable due to dropout or loss to follow-up are assumed to be at least “missing at random” and will be replaced by using multiple imputation. Occurrence of IH after the ICE re-laparotomy affecting the loop ileostomy closure site and death without prior observation of IH will be imputed the same way. Information whether a patient was event-free regarding the occurrence of an IH before loss-to-follow-up, dropout or the respective ICEs will be included into the multiple imputation procedure. This will be done by imputing the primary endpoint “incisional hernia within 24 months” (yes/no) using the variable “incisional hernia within 12 months” (yes/no) besides treatment group, IH risk (high vs. low) and centre using the fully conditional specification (FCS) and the discriminant function method. ICEs that are handled using a treatment policy strategy will be ignored in the primary analysis. The proportion of each ICE will be described by group to support the interpretation of the primary effect estimate.

Sensitivity analyses regarding the imputation method and the underlying assumptions will be performed. These include applying a pattern mixture model under the assumption of a “missing not at random” data mechanism, as well as best- and worst-case scenarios to assess the robustness of the results.

Within a sensitivity analysis, oncologic treatment will be included into the logistic regression model for the primary endpoint as an additional covariate.

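### A parastomal hernia at the closure site is allowed at entry and examined for at screening, but the primary model, the imputation model and the named subgroups do not use it

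*Protocol article*

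**What the plan says.** The lead-in to the inclusion criteria describes eligible patients as "without further interventions or conditions to the abdominal wall, which might interfere with the primary outcome measure". The exclusion list then removes only "Presence of parastomal hernia in loop ileostomy site with fascia defect > 8cm". Table 1 makes this operational. A patient with no hernia on clinical examination can enter, a patient with a confirmed defect above the limit cannot, and unclear cases go to imaging. A smaller parastomal hernia is therefore admitted by design.

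The primary outcome is an incisional hernia at the ileostomy closure site within two years (Outcomes {12}).

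The handling of baseline risk is fixed in the article:
- **Allocation:** "Randomisation will be stratified by centre" (Sequence generation {16a}).
- **IH risk:** high risk means a BMI of 27 or more (Sample size {14}).
- **Primary model:** "including the factors treatment group and IH risk (high vs. low) as fixed effects and centre as a random effect" (Statistical methods {20a}).
- **Imputation:** 12-month hernia status, treatment group, IH risk and centre (same section).
- **Subgroups {20b}:** item (e) is history of hernia or hernia repair. The same history enters the exploratory risk-factor model.

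The Background section states: "Parastomal hernia is frequent after ostomy creation and is estimated to be over 30% by 12 months". The intercurrent-event list gives parastomal hernia as one example of why a patient might need mesh despite allocation.

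**The concern.** An existing fascial defect at the place where the endpoint is read is a plausible baseline predictor of a later gap there. The protocol has this information for every patient, because eligibility turns on it, but does not use it in the primary analysis. Subgroup (e) names neither the site nor a current hernia, so as worded it does not isolate these patients.

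Three things are at stake, none of them the validity of the test:
- precision that a prognostic covariate would give;
- protection against a chance difference between arms in the share of such patients;
- the reader's ability to see how mesh performs in patients with and without a hernia at the site.

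Separately, the lead-in promises the absence of interfering abdominal-wall conditions, which sits uneasily with an exclusion that stops only at larger defects.

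**Working it through.** **1. The plan's own figure.** Inputs from Sample size {14}: 30% vs 15%, two-sided 5%, 80% power. With pooled variance and no continuity correction:

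n = [1.96·√(2·0.225·0.775) + 0.8416·√(0.30·0.70 + 0.15·0.85)]² / 0.15² = (1.157 + 0.489)² / 0.0225 ≈ 120.5, so 121 per group (power 80.2%).

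121 / 0.8 = 151.25, so 152 per group and 304 in total. The stated figures reproduce, and nothing below changes them.

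**2. Chance imbalance.** The documents do not give the prevalence q of parastomal hernia among enrolled patients, so 10–30% is assumed. With 152 per arm, the SD of the between-arm difference is √(2q(1−q)/152), and the probability uses a normal approximation.

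| q | SD (points) | P(gap ≥ 10 points) |
|---|---|---|
| 10% | 3.4 | 0.4% |
| 20% | 4.6 | 2.9% |
| 30% | 5.3 | 5.7% |

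**3. What a 10-point gap does.** Assume an odds ratio of 3 for later hernia and q = 30%.
- Control arm at 30% overall: about 23% without and 47% with a baseline hernia, a difference of 24 points (0.7·23 + 0.3·47 ≈ 30).
- Mesh arm at 15% overall: the corresponding difference is about 15 points.
- With the gap split evenly, 5 points in each arm, the shift is 0.05·24 + 0.05·15 = 1.2 + 0.75 ≈ 2.0 points. If the control-arm difference applied throughout, it would be 0.10·24 = 2.4 points.
- The standard error of the rate difference at 121 per arm is √[(0.30·0.70 + 0.15·0.85)/121] = 5.3 points, so the shift is 2.0/5.3 ≈ 0.4 standard errors, in either direction.

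**4. Power from adjustment.** Simulated logistic regression with 242 patients, marginal rates of 30% and 15%, and 3,000 runs per row:

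| q | OR | Without covariate | With covariate | Gain (points) |
|---|---|---|---|---|
| 10% | 3 | 80.7% | 81.7% | 1.0 |
| 20% | 3 | 79.7% | 81.2% | 1.5 |
| 30% | 3 | 80.5% | 82.8% | 2.3 |
| 30% | 4 | 78.5% | 81.4% | 2.9 |

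The simulation error of one power figure is about √(0.8·0.2/3000) = 0.7 points. At an odds ratio of 2 the gain is at the bottom of the range, at most about 1 point. At an odds ratio of 1 nothing is lost.

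**5. Size of the separate group.** 0.10·304 ≈ 30 to 0.30·304 ≈ 91 patients.

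**6. If the mesh effect differs by baseline hernia.** Assume a risk ratio of 2 for later hernia, control rate held at 30%, and mesh halving the risk in patients without a baseline hernia.
- If mesh also halves it in those with one, power stays at 80%.
- If the relative effect there is 0.75, power is 71/63/55% at q = 10/20/30%.
- If it is 0.3, power is 86/90/93%.

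The documents support neither direction. The calculation shows only that the overall result could depend on a group that the report would not show.

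**The case against.** The strongest reply is that this is a design choice with little consequence. Randomisation protects the comparison, a large imbalance is rare, its effect is under half a standard error, and both prevalence and odds ratio are assumed. All of that stands.

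A reader might also infer more than the documents support:
- **That the estimate is biased.** It is not. Imbalance arises by chance only, in either direction.
- **That the aim is prevention in patients who had no hernia.** The Objectives section compares hernia rates after loop ileostomy closure without that limit, and the estimand defines its population through the eligibility criteria.
- **That the endpoint may already be present at entry.** The definition needs a gap in a postoperative scar, and the fascia is closed in both arms. The parastomal hernia is a risk factor, not an early event.
- **That over 30% of enrolled patients have one.** The Background figure concerns ostomies in general at 12 months, not loop ileostomies at reversal.
- **That the protocol expects mesh to be necessary in these patients.** It says only that switching may be needed, gives this as an example, and plans complementary estimands for switchers.
- **That adding the covariate separates prevention from repair.** A main effect cannot do this. A subgroup with interaction can describe it, but in roughly 30–90 patients.

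It can also be said that the analysis plan may define subgroup (e) more closely, and that further descriptive subgroups are announced. That is possible, but the primary and imputation models are spelled out in the article without this variable. Finally, the lead-in can be read as a general aim that the exclusion list makes operational. That softens the tension but does not remove it.

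**Conclusion.** The concern holds in a limited form. The protocol admits a prognostically plausible condition at the endpoint site, examines for it at screening, and then leaves it out of the stated primary model, imputation model and named subgroups. The test is valid and the comparison unbiased in expectation.

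The cost is modest: about 1–3 points of power at assumed odds ratios of 2–4, and a shift of about 2 points in the rare trial with a 10-point imbalance. The report would also lack separate results by baseline hernia, which matters more for interpretation than the imbalance does. These sizes rest on an assumed prevalence of 10–30% and the assumed odds ratios. The change is worth making because it costs little, not because the trial is at risk without it.

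**What to change.** Before database lock, and without sight of outcomes by arm:
1. Record parastomal hernia at the closure site (yes/no) from the Table 1 examination, if the case report form does not already hold it.
2. Add it as a pre-specified fixed effect in the primary mixed logistic model and as a variable in the imputation model.
3. Report it as its own pre-specified descriptive subgroup, with a treatment-by-subgroup interaction, separate from history of hernia or hernia repair.
4. Reconcile the eligibility lead-in with the exclusion list, so that the target population is described in one way. No position is taken here on which defect size should be eligible.

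Stratification by centre stays: recruitment began in October 2022, and covariate adjustment is the practical route. The sample size is unchanged.

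The cost is protocol and analysis-plan wording and one more model parameter. The covariate rests mainly on clinical examination, with imaging only where unclear, so misclassification would reduce the gain. The subgroup will be small and can only be descriptive.
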